### Recruitment

Obtaining a representative sample of OST patients is essential in determining the HCV prevalence and incidence among OST patients at a national level.

#### Clinician recruitment

In Germany, all clinicians who prescribe opioid substitution medication are registered in the national Substitution Register, a database maintained by the Federal Opium Agency of the Federal Institute for Drugs and Medical Devices (*Bundesinstitut für Arzneimittel und Medizinprodukte, BfArM*). In 2013, the Substitution Register counted 2691 clinicians prescribing opioid substitution medication. Information about clinicians in the Substitution Register is unavailable to the public. To ensure that all OST clinicians in Germany are considered in the present study, study invitations were sent to all substitution medication prescribing clinicians registered in the database of the National Association of Statutory Health Insurance Physicians – in German “Kassenärztliche Bundesvereinigung (KBV)”. The KBV mailed the invitations on our behalf; 524 responses were received, of which 100 were excluded because they did not provide written informed consent, 42 because clinicians did not currently provide OST, and 63 because they treated three or less patients at the time, leaving 319 clinicians for sampling.

#### Sampling method

Official data on the distribution of OST clinicians in Germany (as of 1.07.2013) was obtained from the Substitution Register. This data was stratified according to German Federal State (GFS; in German “Bundesland”) and the number of patients each clinician was treating (Patients Per Clinician, PPC), the latter consisting of four self-defined categories: (I) 4 – 10 PPC, (II) 11 – 40 PPC, (III) 41 – 80 PPC, (IV) 80 or more PPC. When clinicians replied to the study invitation, they were asked to indicate the number of OST patients they attend to, in order to be allocated to a PPC category. Implausible PPC values were identified and corrected in consultation with the corresponding clinician.

Stratified random sampling was performed to preserve the strata proportions of the population of OST clinicians within the sample. The sampling scheme was structured, based on the distribution of the total sample of OST clinicians in Germany, according to GFS and PPC. Using the SPSS Complex Samples procedure, pre-defined random subsamples for every GFS and PPC category were selected from the eligible sample (*n* = 319).

On 11.07.2014, a representative sample of 88 clinicians was drawn to arrive at approximately 2500 patients as planned (Table 1). If clinicians drop out of the study, participants will be re-recruited to meet the representativeness criteria. If several clinicians meet the criteria, SPSS will be used to draw one at random, and if no more clinicians meet the criteria, they will be drawn from the nearest PPC category rather than a different GFS to maintain national representativeness.

**Table 1 Tab1:** Distribution of OST clinicians by German Federal State and patients per clinician

	Distribution of OST clinicians in Germany with a qualification for addiction therapy	Distribution of the preliminary sample of OST clinicians in the present study (as of 11.07.2014)	
German Federal State (GFS)	%	n	%
Baden-Württemberg	13.6	11	12.5
Bayern	9.2	8	9.1
Berlin	6.2	5	5.7
Brandenburg	0.3	1	1.1
Bremen	3.0	3	3.4
Hamburg	4.2	4	4.5
Hessen	9.3	8	9.1
Mecklenburg-Vorpommern	0.6	1	1.1
Niedersachsen	9.9	7	8.0
Nordrhein-Westfalen	32.1	27	30.7
Rheinland-Pfalz	3.1	4	4.5
Saarland	0.8	0	0.0
Sachsen	0.8	2	2.3
Sachsen-Anhalt	1.1	1	1.1
Schleswig-Holstein	4.9	5	5.7
Thüringen	0.9	1	1.1
Total	100.0	88	100.0
Patients per clinician (PPC)	%	*n*	%
4–10	16.7	13	14.8
11–40	44.1	38	43.2
41–80	26.9	24	27.3
>80	12.3	13	14.8
Total	100.0	88	100.0

#### Patient recruitment

Patients of participating clinicians are included in the study if they fulfil the eligibility criteria. To avoid clinicians with a large number of OST patients from dominating the study sample, a maximum of 60 patients per clinician is employed. Thus for each clinician with more than 60 patients, ECHO-study research staff draws a random sample of 60 patients.

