## Methods/Design

### Study design

ECHO is a non-interventional, observational, longitudinal study being conducted between 2014 and 2016 in a large representative sample of approximately 2500 OST patients from about 100 OST clinicians across Germany. Data is collected during routine patient care and from questionnaires administered to patients and clinicians.

At baseline, we examine OST patients’ HCV status to assess HCV prevalence. Also the rate of HCV treatment uptake among OST patients and factors associated with treatment uptake are examined. Patients that are HCV negative at baseline or started HCV treatment up to 12 months prior to baseline are followed up after 12 months to assess the HCV incidence rate, factors influencing seroconversion, and (if applicable) the course of HCV treatment (e.g., treatment outcome, side effects). At both baseline and follow-up, the HCV status will be recorded from the participant’s chart. Clinicians are reminded of the HCV treatment guidelines in Germany, which recommend yearly HCV testing in this high-risk population, to encourage them to perform HCV antibody and/ or HCV RNA testing through the standard of care within the clinics. The study duration is either 1 day or 12 months depending on whether participants take part in the follow-up. Patient recruitment takes place over 12 months, data collection over 18 months, and the total length of the study is 27 months.

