### Planned statistical analysis

HCV prevalence will be calculated based on data from all OST patients at baseline. Additionally, RNA confirmation tests will provide an estimate of the distribution of HCV genotypes and subtypes. To calculate the incidence rate per person-years, the expected subsample of approximately 800 HCV seronegative patients (given a prevalence rate of 68 % anti-HCV seropositive patients, see ‘Sample Size’) will be observed over the course of 12 months. Factors influencing HCV treatment uptake (e.g., physical and mental health) and seroconversion (e.g., concomitant drug use) will be tested by means of bivariate and multivariate analyses (e.g., logistic regression) based on the scale levels of the respective variables. If patients terminate or drop out of OST or no longer wish to participate in the study, the reasons and circumstances will be documented. Dropouts will be analysed in an attempt to identify possible predictors for an early end of treatment.

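### The cap of 60 patients per clinician under-represents patients of large practices in a sample described as representative of OST patients, and the stated prevalence calculation contains no correction for it

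*Protocol article*

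**What the plan says.** The target population is patients. Under Recruitment: "Obtaining a representative sample of OST patients is essential in determining the HCV prevalence and incidence among OST patients at a national level". Study design describes a "large representative sample of approximately 2500 OST patients from about 100 OST clinicians across Germany".

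What the draw makes proportional is clinicians. Under Sampling method: "Stratified random sampling was performed to preserve the strata proportions of the population of OST clinicians within the sample". The strata are Federal State and number of patients per clinician (PPC).

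Within a clinician, Patient recruitment first says "Patients of participating clinicians are included in the study if they fulfil the eligibility criteria" and then sets the limit: "To avoid clinicians with a large number of OST patients from dominating the study sample, a maximum of 60 patients per clinician is employed". The mechanism is random: "for each clinician with more than 60 patients, ECHO-study research staff draws a random sample of 60 patients".

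Under Planned statistical analysis: "HCV prevalence will be calculated based on data from all OST patients at baseline". The article says neither that this figure is weighted nor that it is unweighted. The limitations in the Discussion cover clinician non-response, clinician drop-out and loss to follow-up, but not the effect of the cap.

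**The concern.** Drawing clinicians with equal probability and taking all their patients gives every patient about the same chance of entering the study. The cap breaks this. It is introduced so that large practices do not dominate, but if the estimand is the average over OST patients nationally, large practices should count in proportion to the patients they treat. A capped sample can still estimate that average, provided the known sampling fraction is reversed in the analysis. The article fixes the unequal-probability draw and claims patient representativeness, but nothing it says about the analysis connects the two.

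At stake is the headline result. If prevalence, incidence or treatment uptake differs between large and small practices, a simple pooled figure estimates the average of a capped sample, and a larger sample would not remove the difference. The article gives some reason to think practice size could matter: size is a stratifier, the Background and Discussion report less regular HCV testing in small centres, and HCV status is taken from charts.

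**Working it through.** **The plan's own figures.** Sample size: 32 / 0.04 = 800 antibody-negative patients, and 800 / (1 − 0.68) = 2500. This reproduces, with no term for unequal selection. Table 1: 13/88 = 14.8%, 38/88 = 43.2%, 24/88 = 27.3% and 13/88 = 14.8% for the four PPC categories. These reproduce too.

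**Inputs from Table 1.** Clinicians in Germany by PPC: 16.7% (4–10), 44.1% (11–40), 26.9% (41–80), 12.3% (>80). Clinicians drawn: 13, 38, 24, 13.

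**Assumed inputs, not in the article.** Mean PPC is taken as the category midpoint: 7, 25.5 and 60.5. If sizes are spread evenly over 41–80, the mean after the cap is (50.5 + 60)/2 = 55.25. The mean above 80 is varied from its minimum, 81, to 200.

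**Step 1: inclusion chance.** Relative to a patient in a practice of 60 or fewer, the cap gives 60/M: 0.74 at M = 81, 0.50 at 120, 0.40 at 150. The >80 category was drawn slightly above its clinician share, a factor of 14.8/12.3 = 1.20. Multiplying: 0.74 × 1.20 = 0.89, 0.50 × 1.20 = 0.60 and 0.40 × 1.20 = 0.48. The over-draw offsets the cap only in part. Practices of 61–80 are thinned as well, by 60/61 down to 60/80.

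**Step 2: share of patients in practices above 80.** With m the assumed mean in that category:

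- National share = 12.3·m / (16.7·7 + 44.1·25.5 + 26.9·60.5 + 12.3·m) = 12.3·m / (2868.9 + 12.3·m)
- Listed study share = 13·60 / (13·7 + 38·25.5 + 24·55.25 + 13·60) = 780/3166 = 24.6%

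**Step 3: shift in an unweighted prevalence.** Shift = (study share − national share) × assumed difference in prevalence between practices above 80 and the rest. The table uses a difference of 10 points, with the large practices higher.

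| Assumed mean, >80 | National share | Study share | Shift (points) |
|---|---|---|---|
| 81 | 25.8% | 24.6% | −0.11 |
| 90 | 27.8% | 24.6% | −0.32 |
| 100 | 30.0% | 24.6% | −0.54 |
| 120 | 34.0% | 24.6% | −0.93 |
| 150 | 39.1% | 24.6% | −1.45 |
| 200 | 46.2% | 24.6% | −2.15 |

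The sign reverses if large practices have lower prevalence. The shift doubles for a 20-point difference and is zero for none.

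**Step 4: sensitivity to the assumed means.** With 20 for 11–40 and 50 (49 after the cap) for 41–80, the study share is 780/2807 = 27.8%, against 29.8% to 51.2% nationally. The shift for 10 points runs from 0.20 to 2.34. The top category is under-represented in every scenario tried.

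**Step 5: yardstick.** The simple-random-sample standard error of 68% at n = 2500 is √(0.68 × 0.32 / 2500) = 0.93 points.

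**Step 6: cost of weighting.** The Kish design effect of the category weights is 1.00 at a mean of 81, 1.05–1.06 at 120, 1.11–1.13 at 150 and 1.25–1.27 at 200 (the ranges cover both sets of means). Variation of M within a category would add to this.

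**The case against.** Three stronger readings are tempting, and the article supports none of them.

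- **That the plan specifies an unweighted prevalence.** The analysis sentence names the patients used, in contrast to the seronegative subsample used for incidence. It does not rule out weights, and a journal article may leave weighting to a fuller document.
- **That drawing clinicians in proportion to clinicians is itself the error.** It is not; only the cap creates the imbalance. The over-draw above 80 PPC works against the imbalance. The other departures in Table 1 (none drawn in Saarland, two in Sachsen) are small-integer effects with 88 clinicians in a sample labelled preliminary.
- **That the national estimates are biased, or biased downward.** The article gives no prevalence by practice size. Less regular testing in small centres concerns testing frequency, not prevalence in practices above 60.

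The size can be challenged too. The assumed means give 3166 or 2807 listed patients where the article expects about 2500, so they may be too high; these counts are before eligibility and consent. The yardstick of 0.93 ignores clustering: with 2500/88 ≈ 28 patients per clinician and an assumed intraclass correlation of 0.02–0.05, the standard error is about 1.2–1.4. For incidence, 32 events in 800 person-years give a standard error of √32/800 = 0.71 per 100. Even an assumed difference of 2 per 100 shifts the rate by only about 0.02 to 0.4. Finally, the Discussion already concedes that only 319 of 2691 clinicians were willing and eligible, a threat that weights cannot cure within strata.

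All of this limits the size and certainty of the point. It does not remove the mismatch between a capped draw and a claim of patient representativeness.

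**Conclusion.** The point holds in a limited form. That the cap thins patients of practices above 60 follows from the text, and their under-representation persists across all the mean practice sizes tried. The sample is built to mirror clinicians, so calling it representative of patients is too strong without a correction, and none is stated.

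How far this matters is uncertain. It rests on assumed mean practice sizes and on an assumed outcome difference by practice size, neither of which the article gives. For prevalence, the effect ranges from nothing to about 2.2 points under the main assumptions with a 10-point difference. At top-category means of 120–150 it is about the size of the sampling error. For incidence it is small beside the sampling error. This is a cheap improvement for the study's own stated estimand, not evidence that its results will be wrong.

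**What to change.** In Planned statistical analysis, state that national prevalence, incidence and treatment-uptake estimates use design weights:

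weight = (Register clinicians in the State × PPC stratum ÷ clinicians participating in it) × (clinician's OST patients ÷ patients drawn from that clinician)

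Collapse sparse strata, such as Saarland with no clinician drawn. Use standard errors that allow for clustering by clinician, and report unweighted figures as a sensitivity analysis.

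The inputs are already held: the Register distribution and reported PPC (Sampling method) and the coded patient lists (Procedure). The cost is some programming and a modest loss of precision, the design effects given in the working. No new data are needed.

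If the sponsor prefers not to weight, the alternative is wording: limit the claim of representativeness to clinicians and name the cap among the limitations.

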### Procedure

Once a representative sample of OST clinicians is drawn, written informed consent and coded patient lists are obtained from all clinicians. The codes consist of patients’ initials, date of birth and gender and are used to identify questionnaires when they are sent back to the research centre. Clinicians also indicate which patients started a course of HCV treatment up to 12 months prior to baseline, so that the research staff can send the follow-up questionnaires to the correct patients. If clinicians have more than 60 PPC, research staff draws 60 patients as described above and sends the lists of selected patients back to the clinicians.

Next, study materials are sent and explained to participating clinicians. Data collection begins after patients provide written informed consent. The follow-up phase starts 12 months after study initiation, which may be a different point in time for each patient. In case clinicians do not provide written informed consent, stop communicating to the research staff, or do not collect data, ECHO-study research staff will try to communicate with OST clinicians to understand the reason for their inactivity (e.g., they forgot about the study). If these difficulties are not resolved, the clinician will be excluded and another clinician will be recruited according to the same representativeness criteria.

#### Monitoring framework and quality of data

A 2-level monitoring framework is implemented to improve the quality of data. Monitoring level 1 ensures data completeness. Before data collection begins, ECHO-study research staff briefs clinicians and medical assistants on the study process, explains the material, and trains them in proper documentation. Throughout the study, research staff stays in contact with clinicians and medical staff via telephone calls and personal visits to answer any questions and to ensure participation and complete documentation. Clinicians and medical assistants are responsible for complete and accurate data collection, because data is gathered during routine patient care. Research staff checks the data for plausibility and completeness and may ask clinicians and medical staff to complete or correct missing or implausible data. Research staff merely has access to pseudonymized data at this stage.

In monitoring level 2, extended in-house source data verification (SDV) is conducted to ensure accuracy of recorded data. SDV is performed on 20 % of the patient sample of 25 % of clinicians. The more patients a clinician attends to, the more patients from that clinician are selected for SDV. Trained staff members that are not otherwise involved in the ECHO-study make use of an SDV form and check the data for accuracy. If necessary, they report back to clinicians to clarify and correct implausible or incorrect data entries in the best possible way. All data is stored electronically and safely at the research centre.

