#### Sample size

The sample size calculation is based on the primary outcome variable of HCV incidence among OST patients. The literature reports an HCV incidence of 2–4 per 100 person-years in this target group [32, 33]. For a sample size of (at least) 32 patients with HCV seroconversion and an observation period of 1 year, 800 HCV antibody-negative patients are needed as an initial sample size. Based on previous literature [34], we assume an HCV antibody prevalence of about 68 % among OST patients in Germany. Therefore a sample size of 2500 patients is needed (32 % corresponds to *N* = 800).

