### Variables

Clinician and patient questionnaires are administered at baseline. Medical staff can complete parts of the clinician questionnaire, including objective information (e.g., HCV diagnostics) but not subjective ratings (e.g., problem severity in various life areas). Clinicians will complete the follow-up questionnaire for patients that started HCV treatment up to 12 months prior to baseline and for patients that were HCV negative at baseline. Table 2 provides an overview of all instruments.

**Table 2 Tab2:** An overview of instruments used in the patient and clinician questionnaires

	Sections	Instruments
Patient questionnaire	Sociodemographics	Sociodemographics
	(Health-related) Quality of life	QOL; SF-12
	Physical and mental health	OTI-HSS; BSI-18
	Infectious diseases	Knowledge, needs and attitudes; HCV treatment and treatment experiences
	Autonomy preference	API-Dm
	Satisfaction with care	ZAPA
Clinician questionnaire	Sociodemographics	Sociodemographics
	Physical and mental health	Somatic and psychiatric diseases; CGI
	Routine patient care data	Substitution treatment; HCV diagnostic and treatment; Consumption of substances
	Patient wellbeing	Problem severity in life areas; GAF
Clinician questionnaire (follow-up)	Routine patient care data	Recent HCV treatment; Diagnostics prior to the recent HCV treatment; Current HCV status

*Note*: *QOL* quality of life, *SF-12* 12-Item Short Form Health Survey, *OTI-HSS* Opiate Treatment Index-Health Scale Score, *BSI-18* Brief Symptom Inventory-18, *API-Dm* Autonomy Preference Index - German modified version, *ZAPA* Satisfaction in Outpatient Care – Patient Participation, *CGI* Clinical Global Impression, *GAF* Global Assessment of Functioning

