##### *C. Current HCV status*

The current HCV status is recorded from the participant’s chart. Clinicians are reminded of the HCV treatment guidelines in Germany, which recommend yearly HCV testing in this high-risk population.

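### Source data verification is allocated by practice size with no stated targeting of seroconversions, so only about 1–3 of the 16–32 expected primary events would be checked against source

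*Protocol article*

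**What the plan says.** In the protocol article, Sample size names the outcome that drives the study: "The sample size calculation is based on the primary outcome variable of HCV incidence among OST patients". It gives the expected rate ("The literature reports an HCV incidence of 2–4 per 100 person-years in this target group") and the target: "For a sample size of (at least) 32 patients with HCV seroconversion and an observation period of 1 year, 800 HCV antibody-negative patients are needed". It assumes an antibody prevalence of 68%, which leads to 2500 patients.

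HCV status comes from the chart at both time points (Study design). For follow-up, the article says "The current HCV status is recorded from the" patient's chart (Clinician questionnaire (follow-up), section C). Under Variables, medical staff as well as clinicians may fill in the HCV diagnostics items.

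Monitoring has two levels (Monitoring framework and quality of data):

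- Level 1 covers all data: "Research staff checks the data for plausibility and completeness and may ask clinicians and medical staff to complete or correct missing or implausible data".
- Level 2 is the comparison with source: "SDV is performed on 20 % of the patient sample of 25 % of clinicians". The only stated driver of the allocation is practice size: "The more patients a clinician attends to, the more patients from that clinician are selected for SDV". Staff who carry it out report back so that wrong entries can be clarified and corrected.

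No rule is stated that recorded seroconversions, or baseline-negative records, are verified.

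**The concern.** A seroconversion here is a difference between two transcribed chart entries, and it is rare. Recording errors do not cancel for such an outcome. A true positive entered as negative at baseline joins the at-risk set, is followed up, and becomes a false seroconversion once the correct status is recorded. A true negative entered as positive at baseline simply leaves the at-risk set. With more than twice as many positives as negatives expected, baseline error therefore pushes incidence upward. False events would also blur the analysis of factors associated with seroconversion, since they reflect recording and not infection.

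Verification spread by practice size reaches primary events only in proportion to their share of all patients. Most of the effort goes to records that cannot affect the incidence numerator.

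**Working it through.** **Inputs.** From the article: 2500 patients; 68% prevalence; 800 antibody-negative; 32 events; 2–4 per 100 person-years; verification fractions of 20% and 25%; cap of 60 patients per clinician (Patient recruitment); 88 clinicians drawn (Sampling method). Assumed, because the article gives no figure: a baseline recording error e of 0.5–1% among antibody-positive patients.

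**1. The plan's own figures.** 32 / 0.04 = 800 and 800 / (1 − 0.68) = 2500. Both reproduce. The 32 events need the upper literature rate; at 2 per 100 the same 800 patients give 800 × 0.02 = 16. Expected positives: 2500 × 0.68 = 1700.

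**2. Share of patients verified.**

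- Nominal, if verified practices are of average size: 0.20 × 0.25 = 5%; 0.05 × 2500 = 125 patients.
- Upper bound, if all 22 verified clinicians (25% of 88) are at the cap: 0.20 × 22 × 60 / 2500 = 264 / 2500 = 10.6%.

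**3. Primary events verified** (events × share; chance of none = (1 − share)^events).

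| True events | Expected at 5% | Chance of none at 5% | Expected at 10.6% |
|---|---|---|---|
| 16 | 0.8 | 0.95^16 = 44% | 1.7 |
| 32 | 1.6 | 0.95^32 = 19% | 3.4 |

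**4. Effect of baseline error.** Let r be the true one-year risk and e the share of the 1700 positives that are recorded negative at baseline, escape level 1 and are recorded positive at follow-up. Apparent incidence = (800r + 1700e) / (800 + 1700e).

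| e | False events | r = 2 per 100 | r = 4 per 100 |
|---|---|---|---|
| 0.5% | 8.5 | 24.5 / 808.5 = 3.03 (×1.52) | 40.5 / 808.5 = 5.01 (×1.25) |
| 1% | 17 | 33 / 817 = 4.04 (×2.02) | 49 / 817 = 6.00 (×1.50) |

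Doubling requires 800r / (1 − 2r) false events. That is 16.7 (0.98% of 1700) at 2 per 100, but 34.8 (2.05%) at 4 per 100.

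If 1% is taken instead as a share of the 800 recorded negatives, there are 8 false events. Incidence is then ((800 − 8)r + 8) / 800, which is ×1.49 at 2 per 100 and ×1.24 at 4 per 100.

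**5. What sampled verification would find.** Of 17 misrecorded patients, 17 × 0.05 = 0.85 would be sampled on average, and none with probability 0.95^17 = 42%. At 10.6% coverage the average is 1.8.

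**The case against.** Four counter-arguments deserve weight.

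**The article is condensed.** A monitoring manual may require verification of key endpoints. This stands as a limit on wording: the article states no targeting, and a reader should not infer that none exists. It does not dispose of the point, because the article gives both the coverage and the basis of allocation, and it is that stated allocation which fits the primary outcome poorly.

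**Level 1 may catch some of these errors.** The clinician questionnaire collects anti-HCV and RNA results, viral load, genotype, test dates and past treatment. The patient questionnaire asks separately about hepatitis C status and treatment, and clinicians list recently treated patients (Procedure). A wrong negative could clash with any of these, and implausible data can be queried. So it would be too strong to say that such errors simply pass. However, no such cross-check is specified, and a clash will not always be there to see.

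**Verification is not blind.** A reader might infer that the stated verification can neither detect nor correct false seroconversions. The article does not support that: staff check accuracy and have wrong entries corrected. The defensible statement is that it would find few.

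**Doubling is a corner case.** A reader might also infer that a 1% error doubles incidence across the planned range. It does so only at a true 2 per 100, with the 1% applied to all 1700 positives, none caught at level 1, and all recorded positive at follow-up. At the 4 per 100 behind the planned 32 events, the factor is 1.5.

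**Conclusion.** The point holds as a weakness in how verification effort is placed. It is not a contradiction or an error in the plan. At nominal coverage about 95% of primary events would go unverified, and at the upper bound about 89%.

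The bias figures are conditional. They rest on an error rate that the article does not supply, and on the misrecorded patients both escaping level 1 and being recorded positive later. Any level 1 success, incomplete follow-up, or a wrong status repeated at follow-up would reduce the number of false events. The coverage figures assume that verified patients have their status checked at both time points, which the article does not say; if only one is checked, fewer events are fully verified.

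The direction of the baseline-error bias does not depend on the assumed rate. Because redirecting a modest number of planned checks deals with it, this is best classed as a cheap improvement.

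**What to change.** In the monitoring section, keep the total verification effort and change its placement:

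1. Before a recorded seroconversion enters the incidence numerator, verify its dated baseline-negative and follow-up-positive results against source. A masked laboratory report under the patient code would do.
2. Remove from the at-risk set any patient for whom an earlier positive result is found.
3. Keep the remaining checks as a random sample that includes baseline-negative patients not recorded as seroconverted. Checking recorded events alone can only remove events; this part gives a view of missed ones.

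**Cost.** About 16–50 targeted checks (the upper figure is the 32 + 17 = 49 of the worst case above) out of about 125, leaving about 75–109 random ones, with the same staff and no added patient burden. The general error-rate estimate becomes less precise: its standard error grows by a factor of up to √(125/75) = 1.29. The checks also spread over more practices, which masked reports would ease.
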